| STUDY DESIGN: This is a proof-of-concept Phase II clinical trial with three different groups: two groups will receive antichagasic therapy plus 40 or 80 mg/day of ATO, respectively. The third group will receive a placebo plus antichagasic therapy. Patients will first receive conventional antichagasic treatment for two months. After a washout of two weeks (or until normalization of liver enzymes), treatment with atorvastatin or placebo will be initiated for two months. These doses were chosen to minimize false negative results, thus providing the best hypothesis test and maximizing the pharmacodynamic effect on inflammation and cardiac and endothelial function. In addition, the treatment sequence aims to minimize adverse reactions that could be caused by the eventual combination of antichagasic drugs with atorvastatin. Study subjects will be randomized, and the three groups will be double-blinded (both clinical investigators and subjects will be blinded) to ATO or placebo. However, antichagasic therapy will be open-label. In addition, qPCR and the other laboratory evaluations, as well as ECG and 2D echocardiograms, will be performed with the clinical investigators blinded to ATO or placebo allocation.

As mentioned above, this study will be conducted at four centers: 1) Hospital San Juan de Dios and 2) Hospital Felix Bulnes in Santiago, Metropolitan Region, 3) Hospital [name] in Viña del Mar, and |

4) Hospital San Martin de Quillota, Valparaiso Region.

**ABSTRACT:** Cardiac complications, including heart failure and arrhythmias, are major causes of disability and death in Chagas disease (CD). We postulate that statins ameliorate vascular and cardiac inflammation in patients with chronic CD, contributing to the recovery of endothelial and cardiac function and thereby improving the efficacy of antichagasic therapy.

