**NUMBER OF STUDY CENTERS:**

Four centers:

- 1) Hospital San Juan de Dios and 2) Hospital Felix Bulnes in Santiago, Metropolitan Region, and.
- 3) [name] Hospital in Viña del Mar and 4) San Martín Hospital in Quillota, Valparaíso Region.

These four centers are part of the National Program for the Control of Chagas Disease.

**Duration of participation:** Each subject will participate in the trial for approximately 12 months from signing the informed consent form. After a screening phase of about 14 days, subjects who meet the inclusion criteria and have no exclusion criteria will be randomized to one of the three study groups.

**Duration of the study:** The total duration of patients' participation in the trial will be twelve months, considering two weeks for screening and evaluation according to PCC guidelines and eight weeks of treatment with antichagasic drugs in their respective groups. The administration of ATO and placebo will continue for an additional eight weeks. There will be follow-up visits up to 12 months after initiation of treatment.

**Sample size:** The trial contemplates a sample of 300 patients, randomly assigning 100 patients to each study group:

Atorvastatin 40 mg;

Atorvastatin 80 mg;

Placebo (nutritional supplement in tablets)

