## 9.3. Study description:

This is a proof-of-concept Phase II clinical trial with three different groups: Two groups will receive antichagasic therapy plus 40 or 80 mg/day of ATO. The third group will receive a placebo plus antichagasic therapy. The placebo is justified as long as the patient receives the complete conventional antichagasic treatment; therefore, the management of his Chagas disease is assured. In this clinical trial, the placebo will be a nutritional supplement tablet with an appearance similar to that of ATO. This product was chosen given the potential difficulties in manufacturing a small number of pills since the trial does not have a pharmaceutical industry sponsor capable of manufacturing it under Good Manufacturing Practice standards.

Nutritional supplements do not affect vascular or cardiac inflammatory parameters and therefore do not introduce confounding elements in the comparative analysis with atorvastatin.

Patients will first receive conventional antichagasic therapy for two months. After two weeks (or until normalization of liver enzymes), treatment with atorvastatin or placebo will be initiated for

four months. These doses were chosen to minimize false negative results, thus providing the best hypothesis test and maximizing the pharmacodynamic effect on inflammation and cardiac and endothelial function. In addition, the treatment sequence aims to minimize adverse reactions that could be caused by the eventual combination of antichagasic drugs with atorvastatin. Study subjects will be randomized, and the three groups will be double-blinded (both clinical investigators and subjects will be blinded) to ATO or placebo. However, antichagasic therapy will be open-labeled. In addition, qPCR and the other laboratory evaluations, as well as ECGs and 2D echocardiograms, will be performed with the clinical investigators blinded to ATO or placebo allocation.

This study will be conducted in four centers: 1) Hospital San Juan de Dios and 2) Hospital Felix Bulnes in Santiago, Metropolitan Region, 3) Hospital [name] in Viña del Mar, 4) Hospital San Martin de Quillota, Valparaiso Region. Each center annually admits 60 new patients to its Chagas Control Program (CCP). These four centers are part of the care network of the National Chagas Disease Control Program.

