#### **9.5. Duration of the study and duration of subject participation:**

The total duration of patients' participation in the study will be twelve months, considering two weeks for screening and evaluation according to PCC guidelines and eight weeks of treatment with the antichagasic drugs. The administration of ATO and placebo will continue for an additional eight weeks in their respective groups. There will be follow-up visits up to 12 months after the start of treatment (see appendix for a graphical presentation of the study design).

Following voluntary written informed consent, patients will begin a 14-day evaluation phase. Once the patient is randomized and treatments are initiated, they will have follow-up visits during the treatment phase of the study on days 30, 60, 120, and 180, with a two-week rest period or until normalization of liver enzyme levels ( $\pm$  four-day allowable window), and three visits after the end of treatment (EOT) on days 180, 240 and 360 ( $\pm$  14-day allowable window). In addition, patients will be advised to return on any day during the follow-up period if they have any medical incidents or AEs.

Recruitment is expected to be completed within 24 months from the start of recruitment. Therefore, the time frame between the first patient entering (FPI) and the last patient leaving (LPO) is 36 months. However, the total duration of the study is estimated at 48 months, from the initiation phase to the final study report.

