| Pregnancy test                            | x         |          |           |    |                | x                | x                |     |
| Serology                                  | x         |          |           |    |                |                  |                  | x   |
| Laboratory                                | x         | x        | x         | x  | x              | x                | x                | x   |
| Quantitative PCR                          | x         |          |           |    | x d |                  |                  | x   |
| Biomarkers b                   |           | x        |           | x  | x              |                  |                  | x   |
| Focused Physical Examination c | x         | x        | x         | x  | x              | x                | x                | x   |
| Adverse Events                            |           |          | ←-----→   |    |                |                  |                  |     |
| Drug Accounting                           |           | x        | x         | x  | x              |                  |                  |     |

aLaboratory parameters will include: hemoglobin, total white blood cell count, differential white blood cell count, and platelet count. Laboratory biochemical parameters will include: CK, ALT, AST, GGT, alkaline phosphatase, total and direct bilirubin, a lipid profile: total cholesterol, c-HDL, and c-LDL, triglycerides, fasting blood glucose, and creatinine;

bBiomarkers: BNP, cTnT, IFN-γ, IL-1β, IL-4, IL-17A, e IL-10, sICAM-1, sVCAM-1, sE-selectin;

cPhysical examination focused only on the evaluation of adverse events.;

dPCR testing at these time points will be done with a single 10 ml sample;

eECGs will be performed at these visits only in case of previously identified abnormalities

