### 9.7. Assessments:

On admission to the PCC, patients will undergo a complete medical history with an emphasis on CD, demographic data and medication history, physical examination, body weight and height, vital signs, and body temperature.

Ten ml of blood will be collected, in separate tubes, for hematological and biochemical evaluations: hemoglobin, total and differential white blood cell count, platelet count, CK, ALT, AST, GGT, alkaline

phosphatase, total and direct bilirubin, a lipid profile: total cholesterol, c-HDL, and c-LDL, triglycerides, fasting blood glucose and creatinine. A serum pregnancy test will also be performed. This test will be performed in the clinical laboratories of each center.

A 3 mL blood sample will be collected for conventional CD serology at each center's clinical laboratories and for a confirmatory serology test to be performed at the ISPCCH or an accredited laboratory.

5 mL of blood will be collected for qPCR. For clinical development and proof of concept, it has been proposed to use quantitative PCR parasitological tests as markers of efficacy in clinical studies of chronic indeterminate CD (Parrado et al., 2019). Thus, the real-time PCR technique described by Duffy et al. will be used in this assay (Duffy et al., 2013). Blood samples will be immediately added to a tube containing a volume (10mL) of a solution of guanidine/CIH 6M EDTA 0.2M 0.2M guanidine/CIH buffer 0.2M pH 8.0 (GEB) (Schijman et al., 2003). Samples with guanidine buffer can remain at room temperature for up to 30 days. For longer periods, it is necessary to store them in a refrigerator. After DNA extraction, samples will be processed using a commercial kit on an Applied 155 Biosystems 7300 RT-PCR system (Thermo Fisher).

An additional 3 ml of blood will be drawn for the biomarkers: BNP, cTnT, IFN- $\gamma$ , IL-1 $\beta$ , IL-4, IL-17A, and IL-10, sICAM-1, sVCAM-1, sE-selectin. These markers were selected following a literature review (Cortes-Serra et al., 2020; Echeverría et al., 2020; Llaguno et al., 2019). Serum levels of these markers will be determined using a multiplex approach with a Luminex 200 (R&Dsystems). To establish biological reproducibility, a pilot study will be performed before the sample analyses of this assay.

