Finally, a baseline resting ECG and a 2D echocardiogram will be performed. Both tests will be performed at each center. The ECG should be normal or with nonspecific changes (incomplete right bundle branch block, incomplete left anterior fascicular block, mild bradycardia, minor PR interval widening, and minor ST-T changes). Any clinically significant abnormality found on the electrocardiogram will automatically lead to the exclusion of the patient from this study (see exclusion criteria).

After randomization and before starting treatments, patients will undergo a new focused physical examination, and blood will be drawn for qPCR and biomarker determination.

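### No pregnancy test is scheduled between screening and day 180, so at nominal timing atorvastatin or placebo starts on a result 71 to 88 days old

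*Protocol*

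**What the plan says.** The flowchart in section 6 and the event schedule in section 9.6 agree. The row "Pregnancy test" is marked at Visit 1 (day -14 to -1), Visit 6 (day 180) and Visit 7 (day 240). It is blank at days 0, 30, 60, 120 and 360.

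Three other places could have supplied a test and do not:

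- The laboratory panel repeated at every visit is defined in footnote a: "Laboratory biochemical parameters will include: CK, ALT, AST, GGT, alkaline phosphatase, total and direct bilirubin, a lipid profile", plus glucose, creatinine and blood counts. It has no pregnancy test.
- Section 9.7 lists one test, with the admission bloods: "A serum pregnancy test will also be performed". After randomization and before treatment, that section adds a focused examination and states that "blood will be drawn for qPCR and biomarker determination".
- The rule for starting the randomized drug reads, in the section 6 summary, "After a washout of two weeks (or until normalization of liver enzymes), treatment with atorvastatin or placebo will be initiated for two months". Section 9.3 says "After two weeks (or until normalization of liver enzymes), treatment with atorvastatin or placebo will be initiated for" four months. Neither mentions pregnancy.

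Sections 10.1 and 10.2 require a negative serum test at entry for women of reproductive age, exclude pregnant and breastfeeding women, and require highly effective contraception while treatment lasts.

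**The concern.** The randomized drug does not start at randomization. It starts after a full antichagasic course and a rest period, so the entry test is more than two months old by then. The protocol makes the start wait for liver enzymes but asks for no fresh look at pregnancy, although either can change in that time.

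A woman who conceives in the 10 to 12 weeks after screening would, if the schedule is followed as written, begin atorvastatin or placebo with no scheduled test able to show it. Participants are adults under 50, pregnancy is an exclusion, and section 11.2.2 counts a congenital anomaly as a serious adverse event. The protocol accepts that testing after entry is needed, since it schedules two later tests. Both are placed late in dosing or after it.

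This is a participant-safety point. It does not touch the primary outcome, the randomization or the efficacy analysis.

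**Working it through.** The protocol states no figure for the age of the test, so this is calendar arithmetic from its own timings.

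**Inputs**

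- Screening test: day -14 to day -1 (sections 6 and 9.6).
- Antichagasic course: "eight weeks of treatment with the antichagasic drugs" in section 9.5 (and "eight weeks of treatment with antichagasic drugs in their respective groups" in section 6), which is 56 days; or 60 days (section 7.1.4, consistent with two months in section 9.3).
- Rest period: 14 days, or longer until liver enzymes normalize (sections 6, 9.3 and 9.5), with a four-day window in section 9.5.
- Atorvastatin/placebo course: eight weeks (section 9.5), or four months (section 9.3), the latter matching the 120-tablet bottle at one tablet a day (section 11.1.1).

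**Start of the randomized drug** = antichagasic days + 14

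- 56 + 14 = day 70
- 60 + 14 = day 74

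**Age of the last test at the start** = start day + 1 (screened on day -1) to start day + 14 (screened on day -14)

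- Day 70: 71 to 84 days
- Day 74: 75 to 88 days

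The nominal range is therefore 71 to 88 days. Applying the four-day window to the rest period gives starts from day 66 to day 78, so 66 + 1 = 67 to 78 + 14 = 92 days. Slow enzyme recovery lengthens it further.

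**Gap between the first two scheduled tests**: 180 + 1 = 181 to 180 + 14 = 194 days.

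**Where day 180 falls relative to dosing**

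| Course wording | Last dose | Day 180 test |
|---|---|---|
| Eight weeks | 70 + 56 = 126 to 74 + 56 = 130 | After the course |
| Four months (120 tablets) | 70 + 120 = 190 to 74 + 120 = 194 | 180 - 74 = 106 to 180 - 70 = 110 days in |

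**With a test at day 60**

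- Age at start: 70 - 60 = 10 or 74 - 60 = 14 days. With the visit anywhere from day 56 to 64: 70 - 64 = 6 to 74 - 56 = 18 days.
- Longest remaining gap between tests: 180 - 60 = 120 days.
- Tests inside the course: unchanged, none on the eight-week wording and one on the four-month wording. The gain is the check before the first dose.

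**The case against.** The strongest reply is that the protocol is not the whole picture. Antichagasic treatment follows a national manual that is not shown, and that course fills 56 to 60 of the days in question. The manual may call for testing, and any such test would shorten the real gap. The design diagrams and the appendix mentioned in section 9.5 are also not available. This stands as a limit: the point concerns what the protocol schedules, and nothing is claimed about practice during the antichagasic course. It does not answer the point, because the protocol ties no test from the manual or elsewhere to starting atorvastatin or placebo.

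Second, contraception is mandatory, participants are interviewed and examined for adverse events at each visit, and investigators may stop treatment for any medical reason. These reduce the risk and keep the point from being graver. They do not replace a test, and the protocol does not rely on them alone elsewhere.

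Third, the protocol describes no harm of atorvastatin in pregnancy and gives no pregnancy rate, so the number of women affected cannot be estimated. That is correct. The point rests on the protocol's own exclusion and contraception rule, and its size is in days only.

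Fourth, the later figures are softer than they look. Section 9.5 also lists day 180 as a post-treatment visit with a 14-day window, so that test could fall on day 166 to 194, which is 166 - 74 = 92 to 194 - 70 = 124 days after the first dose. On the four-month wording it might even miss the course. This is fair, and does not help the schedule.

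Finally, a day-60 test is not a test at first dose, and a conception around or after day 60 could still be missed. That is true. Neither table has a visit at the start of dosing, so day 60 is the closest existing contact.

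**Conclusion.** The point holds and should be fixed. At nominal timing the randomized drug starts on a pregnancy test 71 to 88 days old, and the next scheduled test comes either after the course or 106 to 110 days into it. This assumes the schedule is followed as written, the rest period lasts two weeks, and no test is added under the national manual or local practice. The conclusion is the same under either stated antichagasic length and either stated atorvastatin length. The risk is partly mitigated by the entry test and contraception, which cover the antichagasic start better than the start of the randomized drug.

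**What to change.** In both schedule tables (sections 6 and 9.6), mark a pregnancy test at the day-60 visit. In section 9.3 or 11.1.1, add a rule such as:

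> In women of reproductive age, atorvastatin/placebo is dispensed or started only after a negative pregnancy test at day 60. If the start is delayed beyond two weeks, the test is repeated on the blood drawn to confirm liver-enzyme normalization.

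The words *or started* matter because section 12.2 can be read as handing over the treatment package at enrollment.

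Keep the day-180 and day-240 tests. On the four-month wording day 240 is 240 - 194 = 46 to 240 - 190 = 50 days after the last dose, inside the two-month observation period of section 11.2.1. It falls during dosing if the start slips past 240 - 120 = day 120. A further test at day 120 is optional.

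The cost is one mark in each of two tables and one short rule. No visit is added: laboratory blood is already drawn at day 60, and waiting for enzymes to normalize already implies a recheck draw, although neither table has a column for it. Each woman of reproductive age has one extra test, plus one repeat if her start is delayed. The protocol does not give the share of such women. Assuming 30% to 70% of 300 patients, that is 0.30 x 300 = 90 to 0.70 x 300 = 210 extra tests, before repeats and dropouts.

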## **11. Subject treatments**

### **11.1.1. Doses and treatments regimens**

Tablets of 40 and 80 mg of ATO will be purchased from a pharmaceutical laboratory with current sanitary registration recognized by the ISPCH, offering the active ingredient in a bioequivalent formulation. The placebo tablets will correspond to a nutritional supplement tablet supplied by a registered provider.

The purchase will be made through the Pharmacy of the Clinical Hospital of the University of Chile.

The ATO and placebo tablets will be repackaged in black plastic bottles of 200 ml capacity, previously sterilized with UV light, under aseptic conditions using a type II biosafety hood. The bottles will contain 120 tablets each and all from the same lot to allow the traceability of the drug.

The labeling of each bottle will be done as required by good manufacturing practices, including a) name and contact information (telephone and e-mail) of the principal investigator; b) dosage form, route of administration, number of units; c) lot number and code (assigned by the principal investigator) of the supplier laboratory; d) project code; e) instructions for use; g) randomization code; f) warning: "for clinical trial use only"; h) expiration date; i) the phrase: "Keep out of the reach of children."

The antichagasic drugs NFX or BZD will be supplied by the Chilean Ministry of Health as part of the PCC. The antichagasic treatment will be administered according to the indications of the "Manual de Procedimientos para la Atención de Pacientes con Chagas" (MINSAL, 2017), and the administration of ATO, antichagasic drugs, and placebo treatment will be monitored at each of the patients' visits to determine tablet accounting and compliance with the drugs. BZD dosing will be 5 mg/kg/day every 12 hours (BID), and NFX dosing will be 5-10 mg/kg/day BID. ATO doses will be 40 and 80 mg/day for each group and will be administered in the morning.

At each visit, the patient will be required to bring all remaining study medications at the 30th, 60th, 120th, and 180th-day visits to check compliance with the prescribed antichagasic and experimental treatment and perform medication accounting (Torrico et al., 2018). **If a subject develops**

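### The blinded atorvastatin/placebo course lasts two months in some sections and four in another, and section 12.1 sets its response at an end of treatment where the echocardiogram is never scheduled

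*Protocol*

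**What the plan says.** **Duration.** The Summary (study design) states that "treatment with atorvastatin or placebo will be initiated for two months". Its paragraph on study duration says "The administration of ATO and placebo will continue for an additional eight weeks", and section 9.5 repeats this: "The administration of ATO and placebo will continue for an additional eight weeks in their respective groups". Section 9.3 describes the same sequence as the Summary but ends the course at "four months. These doses were chosen to minimize false negative results". Section 11.1.1 adds "The bottles will contain 120 tablets each and all from the same lot". The Summary gives atorvastatin once daily. The number of bottles per patient is not stated.

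**Start.** The blinded course follows two months of antichagasic drug (eight weeks in section 9.5) and a washout of two weeks, or longer if liver enzymes have not returned to normal. Visit days are counted from day 0, not from the first blinded dose.

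**Visits.** Section 9.5 names days 30, 60, 120 and 180 as treatment-phase visits and then "three visits after the end of treatment (EOT) on days 180, 240 and 360". Section 11.1.1 asks patients to "bring all remaining study medications at the 30th, 60th, 120th" and 180th-day visits, but the drug accounting row in section 9.6 ends at day 120.

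**Measurements (section 9.6).** Biomarkers, including BNP and cTnT, are drawn on days 0, 60, 120 and 360. Echocardiograms are done at screening and day 360. ECGs are done at screening and on days 60, 120 and 360; for days 180 and 240 the footnote reads "ECGs will be performed at these visits only in case of previously identified abnormalities".

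**Time point.** Section 12.1 assumes response rates of 0.40 and 0.20 for ECG and echocardiographic parameters with BNP and cTnT, at EOT. Section 9.1 sets the primary outcome at 12 months.

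**The concern.** The length of the experimental treatment is a basic design parameter, and the current text gives two values for it. EOT, the adherence denominator and the meaning of each post-baseline measurement all depend on it. The schedule also does not settle where EOT lies: day 180 is on both sides of it, and tablets taken after day 120 are counted in one section and not in another. Section 12.1 then uses EOT as the time point for its planning assumption, although one named component is not measured near that time on either reading. The sample size therefore rests on rates at a time that is neither the primary time point nor a time at which the composite can be observed.

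**Working it through.** **Inputs.** Antichagasic phase A = 56 days (eight weeks, section 9.5) or 60 days (two months, Summary and section 9.3). Minimum washout W = 14 days. Blinded course D = 56 or 60 days (eight weeks or two months), or 112 or 120 days (four months of 28 or 30 days).

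**Formulas.** First blinded dose S = A + W. Last dose E = S + D. Time on blinded drug at day 120 = 120 − S. Gaps: E − 120 and 360 − E.

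| A | D | S | E | Days on drug at day 120 (share of D) | E − 120 | 360 − E |
|---|---|---|---|---|---|---|
| 56 | 56 | 70 | 126 | 50 (89%) | 6 | 234 |
| 56 | 60 | 70 | 130 | 50 (83%) | 10 | 230 |
| 60 | 56 | 74 | 130 | 46 (82%) | 10 | 230 |
| 60 | 60 | 74 | 134 | 46 (77%) | 14 | 226 |
| 56 | 112 | 70 | 182 | 50 (45%) | 62 | 178 |
| 56 | 120 | 70 | 190 | 50 (42%) | 70 | 170 |
| 60 | 112 | 74 | 186 | 46 (41%) | 66 | 174 |
| 60 | 120 | 74 | 194 | 46 (38%) | 74 | 166 |

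**Day 120.** The layout works only without the washout: 60 + 60 = 120. With it, day 120 precedes the last dose by 6-14 days or by 62-74 days. If the four-day window in section 9.5 applies to this visit, it reaches day 124, which is 126 − 124 = 2 days short at best. Each further week of washout removes 7 of the 46-50 days of exposure.

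**Day 180.** On the shorter reading it is 180 − 134 = 46 to 180 − 126 = 54 days after the last dose, so it is not a treatment-phase visit. On the longer reading it is nominally 182 − 180 = 2 to 194 − 180 = 14 days before the last dose, so it is not a visit after EOT except by using the 14-day window (180 + 14 = 194).

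**The section 12.1 components against the schedule.**

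| Component | Day 120 | Day 180 | Day 360 |
|---|---|---|---|
| ECG | yes | only if earlier abnormality | yes |
| Echocardiogram | no | no | yes |
| BNP, cTnT | yes | no | yes |

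Only day 360 has every component, and it is 226-234 days (shorter reading) or 166-178 days (longer reading) after the last dose.

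**Supply.** At one tablet daily, one bottle of 120 lasts 120 days, which matches four months and is twice a 60-day course. Without the number of bottles per patient, this does not settle the duration.

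**The case against.** The best defence is that day 120 is the intended EOT visit. It carries biomarkers, ECG, chest X-ray, a complete physical examination, qPCR and the schedule's last drug accounting. On the shorter reading it is only 6-14 days early, and with a window as little as 2. That stands in part: a reader might infer that the effect on treatment is never measured near its end, but on the shorter reading the biomarkers are measured after most of the course. The gap is large only on the longer reading.

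Second, section 12.1 is a planning assumption and does not define the outcome. Sections 8.1 and 9.1 fix the outcome at 12 months, and at day 360 ECG, echocardiogram, chest X-ray, BNP and cTnT are all scheduled. This also stands: a reader might infer that the primary outcome cannot be assessed, and that is wrong. What remains is that section 12.1 and section 9.1 name different times.

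Third, a reader might infer that centers will give courses differing twofold. The documents do not support this. Bottles are uniform, and each center receives packages tied to a central randomization list. Likewise, little or no exposure at day 120 would need roughly six to seven extra weeks of washout, and the protocol gives no figure for how long washouts will be.

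Finally, the design diagrams are not visible in the text reviewed and may show an intended EOT. They could indicate which reading was meant but would not remove the conflict between sections.

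**Conclusion.** The point holds. The blinded course has two durations in current text, eight weeks or two months against four months, and the last dose shifts from about day 126-134 to about day 182-194 accordingly. Day 180 is classified in two incompatible ways, drug accounting ends on two different days, and section 12.1 refers to EOT while section 9.1 refers to 12 months. The missing echocardiogram at EOT holds on every reading. The distance of the biomarker draw from EOT depends on the reading: modest on the shorter, substantial on the longer.

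The day counts assume the minimum 14-day washout, 56 to 60 antichagasic days, no interruptions, and months of 28 to 30 days. A longer washout moves EOT later and reduces exposure at day 120. No effect on power is claimed, because the protocol gives no response rates at other times. The duration conflict must be resolved because it determines what treatment is delivered; the other items follow from it.

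**What to change.** 1. Reconcile the duration of the blinded course, and the bottle count per patient, across the Summary and sections 9.3, 9.5 and 11.1.1. No view is taken here on which duration is right.
2. State one EOT, defined by the last blinded dose, and remove day 180 from one of the two lists in section 9.5.
3. Extend the schedule's drug accounting to the last-dose visit so that it agrees with section 11.1.1.
4. Make section 12.1 refer to the time point in section 9.1, 12 months, where all its components are measured, and confirm that the assumed 0.40 and 0.20 are meant for that time.
5. Time the day-120 visit from the first blinded dose so that it falls at the last dose. Keep the biomarker draw, qPCR and ECG together: section 9.1 relates biomarker change to parasite load, so moving the biomarkers alone would break that pairing.

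The cost is a protocol amendment and a revised schedule. No new blood draw or imaging is needed. The drawback is that calendar visit days will vary between patients with the length of washout.
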